### Trial design

2.1

This study is a single-center, single-blind, randomized controlled superiority trial. A total of 90 eligible participants diagnosed with CFS with a spleen–kidney yang deficiency pattern will be enrolled. Participants will be randomly assigned in a 1:1 ratio to receive either Jianqiao ancient moxibustion or moxa box moxibustion. The study will span 16 weeks, comprising a 4-week treatment period and a subsequent 12-week follow-up phase.

The trial is registered with the Chinese Clinical Trial Registry (ChiCTR2300079165). The trial flowchart is illustrated in Figure 1, and a detailed timeline is provided in Table 2.

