### Blinding

2.6

Due to the obvious differences in moxibustion devices and procedures, blinding of participants and practitioners is infeasible. To mitigate bias associated with awareness of treatment allocation, outcome evaluators and data statisticians will remain blinded throughout the trial. In addition to patient-reported outcomes, infrared thermal imaging will be utilized as an objective secondary outcome measure to minimize subjective assessment bias. Unblinding will be permitted solely in the event of severe adverse events or upon the completion of data analysis.

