#### Primary outcome

2.8.1

The primary outcome measure will be the Fatigue Scale-14 (FS-14). The FS-14 is a validated 14-item questionnaire for evaluating physical and mental fatigue. Each item utilizes a dichotomous yes-or-no response format and is scored as 0 or 1, with a total score ranging from 0 to 14. Higher scores will indicate more severe chronic fatigue (21, 22). FS-14 assessments will be performed at baseline, week 4 (post-intervention), and week 16 (follow-up).

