### Statistical analysis

2.12

To mitigate subjective bias, all statistical analyses will be conducted independently by two blinded statisticians utilizing SPSS version 22.0. These statisticians will remain uninformed of group allocations and intervention specifics. The intention-to-treat (ITT) analysis set will include all randomized participants who complete the baseline assessment and receive at least one intervention session, and this set will be used for the primary efficacy analysis. The per-protocol (PP) analysis set will include subjects with good treatment adherence, no significant protocol deviations, and complete outcome data and will be utilized for sensitivity analysis to assess the robustness of the research findings. Data collected at multiple time points will be analyzed using a mixed-effects model for repeated measures, including group, time, and their interaction effects, to evaluate inter-group and temporal differences. Missing data will primarily be addressed through multiple imputation, supplemented by the last observation carried forward method for sensitivity analysis, to minimize bias resulting from data attrition. Covariates such as age, sex, disease duration, and baseline FS-14 scores will be adjusted for in the model to correct for confounding bias due to baseline imbalances. The Bonferroni correction will be employed to adjust for multiple comparisons, thereby controlling for the inflation of Type I error rates associated with simultaneous evaluations of multiple secondary outcomes. Treatment adherence will be quantified as the ratio of sessions actually completed to the total number of sessions planned; statistical comparisons of adherence between groups will be conducted, supplemented by additional sensitivity analyses stratified by adherence status. Continuous data exhibiting normal distribution will be analyzed using the *t*-test, whereas data not conforming to a normal distribution will be assessed via non-parametric rank-sum tests. Categorical variables will be compared using the chi-square test or Fisher’s exact test, as appropriate. All statistical tests will be two-tailed, with a significance threshold set at *a p*-value of < 0.05.

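### LOCF and adherence-stratified comparisons do not adequately test robustness to non-random dropout; delta-adjusted multiple imputation should replace LOCF as the sensitivity analysis

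*Protocol article*

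**What the plan says.** Section 2.12 analyses repeated measurements with a mixed-effects model in the set it calls intention-to-treat. On missing data it names multiple imputation as the main method, "supplemented by the last observation carried forward method for sensitivity analysis". On adherence it states: "Treatment adherence will be quantified as the ratio of sessions actually completed to the total number of sessions planned". A between-group comparison of adherence follows, "supplemented by additional sensitivity analyses stratified by adherence status". A third check is the per-protocol set, which requires good adherence and "complete outcome data and will be utilized for sensitivity analysis to assess the robustness of the research findings".

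Three other facts bear on the point:

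- Section 2.1 describes the study as "comprising a 4-week treatment period and a subsequent 12-week follow-up phase".
- Section 2.8.1 schedules the FS-14 only at baseline, week 4 and week 16, and singles out neither later visit as the primary time point.
- Section 2.6 says that "blinding of participants and practitioners is infeasible".

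**The concern.** Multiple imputation in its usual form and the mixed model both rest on data being missing at random. A sensitivity analysis for that assumption should move away from it by a known amount and show when the conclusion changes. LOCF does not do this. It puts in one fixed value per participant, on the premise that nothing changed after the last visit, and treats that value as observed. Here the last visit before week 16 is the end of treatment, so the premise must hold over 12 weeks without treatment.

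Adherence is measured after randomisation, by people who know their allocation. If adherence depends on both arm and prognosis, participants in the same adherence stratum are not comparable between arms. The per-protocol set has the same selection problem, and it also removes participants with missing outcomes.

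At stake is what the checks are taken to mean. Agreement between multiple imputation and LOCF could be reported as robustness although missing at random was never varied in a controlled way. Disagreement would be equally hard to interpret.

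**Working it through.** **Inputs from the article (section 2.11).** Post-treatment FS-14 4.86 (SD 1.43) and 6.23 (SD 2.73); d = 0.63; two-sided alpha 0.05; power 0.80; 10% dropout; 40 per group, raised to 45.

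**The article's own figure.** Difference = 6.23 − 4.86 = 1.37. Pooled SD = √((1.43² + 2.73²)/2) = 2.179. d = 1.37/2.179 = 0.629. The normal-approximation sample size for d = 0.63 is 40 per group, and 40/0.90 = 44.4, rounded up to 45. The stated figures reproduce, and nothing below changes them.

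**Inputs that are assumptions.** The share of the week-4 difference that remains at week 16, the loss in each arm, the control rebound, the baseline FS-14 and the adherence model. All differences are control minus Jianqiao, so a positive value favours Jianqiao.

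**1. Loss after week 4, equal in both arms, at random.** Let m be the share missing week 16 and f the share of the 1.37 points still present then.

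LOCF difference = (1 − m) × f × 1.37 + m × 1.37, so bias = m × (1 − f) × 1.37.

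| f | m = 10% | m = 20% |
|---|---|---|
| 1 (fully kept) | 0 | 0 |
| 0.5 | 0.07 | 0.14 |
| 0 (fully lost) | 0.14 | 0.27 |

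**2. Loss after week 4, unequal.** Suppose controls rebound by 1.5 points and the difference is fully lost, so both arms stand at 6.23 + 1.5 = 7.73 at week 16. Carrying week 4 forward understates a missing Jianqiao score by 7.73 − 4.86 = 2.87 and a missing control score by 1.50. The true difference is 0.

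LOCF difference = 2.87 × m(Jianqiao) − 1.50 × m(control).

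| Jianqiao / control loss | LOCF difference |
|---|---|
| 10% / 10% | 0.287 − 0.150 = 0.137 |
| 20% / 20% | 0.574 − 0.300 = 0.274 |
| 20% / 10% | 0.574 − 0.150 = 0.424 |
| 10% / 20% | 0.287 − 0.300 = −0.013 |
| 5% / 15% | 0.144 − 0.225 = −0.08 |

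The largest value is 0.424/1.37 = 31% of the planning difference. Reversing the losses removes it.

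**3. Loss before week 4.** LOCF carries baseline. With equal baselines and 10% loss per arm, the week-4 difference becomes 0.90 × 1.37 = 1.23, which is conservative. With 5% versus 15% loss and an assumed baseline of 8 to 10, it ranges from 0.79 (Jianqiao loses more, baseline 10) to 1.68 (control loses more, baseline 10).

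**4. Size against sampling error.** With SD 2.18 and 45 per arm, SE = 2.18 × √(2/45) = 0.46. As a rough normal approximation, shifts of 0.137, 0.274 and 0.424 raise the false-positive rate of a 5% LOCF test at week 16 to about 6%, 9% and 15%.

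**5. Adherence strata when treatment has no effect.** This was simulated with a latent severity that drives both adherence and FS-14.

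- Same adherence mechanism in both arms: difference within strata about 0.
- Adherence about 76% versus 66%, same dependence on severity: spurious differences of 0.11 to 0.13 points, with the direction set by which arm adheres more.
- Dependence on severity differing by arm: +0.31 among adherers and −0.74 among non-adherers.

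**The case against.** The strongest reply is that the harm is small and sits in a supplementary analysis. At the planned 10% loss, equal by arm, the week-16 shift is at most about 0.14 points against a standard error of 0.46, and it needs the effect to vanish entirely. Waning, rebound and unequal loss appear nowhere in the article. The week-4 comparison is untouched by carrying week-4 scores forward. All of that stands.

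A reader might infer that LOCF would create a lasting benefit and then confirm the primary result. The calculations do not support this. They assume random dropout, under which properly specified multiple imputation is valid and would show about zero at week 16. LOCF would then contradict the primary result. The calculations show that LOCF adds its own distortion; they do not measure bias under informative dropout.

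A reader might also infer that these checks can show nothing about robustness. That goes too far. Carrying baseline forward for early dropouts is itself a departure from missing at random, and often an unfavourable one. Its size, however, is set by the baseline score and by which arm loses more, and is not chosen and reported as a departure.

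Finally, an analysis plan that is not shown may contain more, so the absence of a tipping-point analysis is not in itself a fault. The point does not depend on that absence: the article names LOCF as the sensitivity method for missing data, and that choice suits the purpose poorly.

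**Conclusion.** The point holds in limited form. LOCF, the adherence strata and the per-protocol set do not adequately test robustness to non-random dropout. LOCF bias at week 16 is nil if the effect persists. If the effect is wholly lost, it is about 0.14 points at 10% loss per arm and 0.27 at 20%. Under unequal loss with the assumed rebound, it runs from about 0.42 in favour of Jianqiao to about zero, or slightly against Jianqiao. Bias from early dropouts can go either way. Adherence strata mislead only if adherence depends on arm together with prognosis, which is plausible with unblinded participants but not established.

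The primary multiple-imputation estimate and the sample size are not affected. The change is worth making because it is cheap and the present checks could give false reassurance.

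**What to change.** Replace LOCF as the sensitivity analysis by delta-adjusted multiple imputation, using the imputations already planned. Add 0, 0.5, 1.0, 1.5 and 2.0 FS-14 points to the imputed Jianqiao values, keep control at missing at random, and report the delta at which significance is lost, or that it is not lost within this range. Each step moves the Jianqiao mean by delta times the share imputed (for example 2.0 × 0.10 = 0.20 points), so the departure is explicit. LOCF may stay as a supplementary result at most.

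Report adherence by arm descriptively. Label any adherence-stratified comparison exploratory and non-randomised, and say that the per-protocol analysis shares this limitation. A complier-average effect is not a suitable substitute, because both arms are active and adherence can be partial in either.

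Cost: a few further runs and one more table. No new data or participants are needed, and the sample size does not change.

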### Sample size calculation

2.11

Sample size was determined by a previously published randomized controlled trial examining the effects of Governor moxibustion on patients with spleen–kidney yang deficiency pattern CFS, utilizing the FS-14 as the primary outcome measure (29). In that study, the post-treatment FS-14 scores were reported as 4.86 ± 1.43 for the moxibustion group and 6.23 ± 2.73 for the control group. The resulting Cohen’s d was 0.63, signifying a moderate effect size. To achieve a two-tailed significance level (*α*) of 0.05 and a statistical power of 0.80, the required sample size is determined to be 40 participants per group. Accounting for an anticipated 10% dropout rate, a total of 45 participants will be recruited per group, resulting in an overall sample size of 90 patients.

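### Optional improvement: Holm's step-down procedure would give the secondary outcomes the same guaranteed error control as the planned Bonferroni correction, with equal or better power

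*Protocol article*

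**What the plan says.** Section 2.12 (Statistical analysis) of the protocol article states that "The Bonferroni correction will be employed to adjust for multiple comparisons". It gives the purpose as limiting the type I error inflation "associated with simultaneous evaluations of multiple secondary outcomes". The same section makes all tests two-sided at 0.05.

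The secondary outcomes in section 2.8.2 are the Spleen–Kidney Yang Deficiency Symptom Scale, the SDS, the SAS and infrared thermal imaging. Section 2.3 states a secondary hypothesis that covers all of these domains together.

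Section 2.11 sizes the trial on the FS-14 alone. It takes "4.86 ± 1.43 for the moxibustion group and 6.23 ± 2.73 for the control group" from a previous trial, states that Cohen's "d was 0.63, signifying a moderate effect size", and arrives at 40 per group before dropout. The article claims no power for any secondary outcome.

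**The concern.** Bonferroni compares every p-value with 0.05/m, where m is the number of tests in the family. Holm orders the p-values and compares the smallest with 0.05/m, the next with 0.05/(m − 1), and so on, stopping at the first failure. Its first threshold is Bonferroni's and the later ones are larger, so it can never reject less. It holds the same family-wise level whatever the correlation between outcomes.

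Because the article names a specific procedure, this is not a request for detail that a statistical analysis plan would supply. At stake is power on the secondary outcomes. If several of the hypothesised secondary effects are real, single-step Bonferroni will miss some that Holm would confirm at the same guaranteed error level.

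**Working it through.** **1. The plan's own figure.** Pooled SD = √((1.43² + 2.73²)/2) = 2.179. The difference is 6.23 − 4.86 = 1.37, so d = 1.37/2.179 = 0.629, which agrees with the stated 0.63. With two-sided α = 0.05 and power 0.80, the normal-approximation formula gives 40 per group, and 40/0.90 = 44.4, rounded up to 45. Section 2.11 reproduces.

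**2. Bonferroni does its stated job.** For independent tests, family-wise error is 1 − (1 − α′)^m.

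| m | Uncorrected, α′ = 0.05 | Bonferroni, α′ = 0.05/m |
|---|---|---|
| 4 | 0.185 | 0.049 |
| 7 | 0.302 | 0.049 |
| 14 | 0.512 | 0.049 |

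**3. Assumptions for the comparison.**
- Family size: 4 is the number of named secondary outcomes. Counting three jiao regions and the Governor Vessel separately gives 3 + 4 = 7. Testing each of these at both post-baseline visits gives 14. The article does not state m.
- Analysable patients: 40 per arm (section 2.11).
- Effect: d = 0.63 for each real secondary effect, borrowed from the FS-14, with 0.5 as a lower value.
- Correlation between test statistics: 0.5, with 0 as a check.

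**4. Bonferroni power per real effect, m = 4.** The non-centrality is 0.63 × √(40/2) = 2.817. The critical value at 0.05/4 = 0.0125 two-sided is 2.498. Power = Φ(2.817 − 2.498) = Φ(0.320) = 0.625. This does not depend on how many of the other effects are real.

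**5. Holm power, m = 4.** The thresholds are 0.0125, 0.0167, 0.025 and 0.05. Simulated correlated normal test statistics (correlation 0.5, d = 0.63) give:

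| Real effects | Average power, Bonferroni | Average power, Holm | All real effects confirmed, Bonferroni | All real effects confirmed, Holm |
|---|---|---|---|---|
| 4 of 4 | 62.5% | 71.5% | 32% | 53% |
| 3 of 4 | 62.5% | 67.5% | 38% | 49% |
| 2 of 4 | 62.5% | 65% | 47% | 51% |
| 1 of 4 | 62.5% | 62.6% | 62.5% | 62.6% |

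The chance of at least one true rejection is practically the same for both methods (88.9% for each with all four real).

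**6. Sensitivity, all effects real.**
- m = 4, correlation 0: average power 63% (Bonferroni) against 73% (Holm).
- m = 4, correlation 0.5, d = 0.5: 40% against 47%.
- m = 7, correlation 0.5, d = 0.63: 55% against 66%.
- m = 14, correlation 0.5, d = 0.63: 46% against 57%.

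**7. Error under both methods, m = 4, correlation 0.5.** With no real effect the family-wise error is identical (about 4.3%). With three of four effects real it is 1.2% for Bonferroni and 3.2% for Holm. Both stay below 5%; Holm's gain comes from error allowance that Bonferroni leaves unspent.

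**The case against.** The strongest reply is that nothing is wrong with the plan. Bonferroni is valid, prespecified and conservative, and step 2 shows that it achieves the purpose the article gives it. The article promises no secondary power. All of this stands, so a reader who infers that section 2.12 contains an error would be going beyond the document.

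The size of the gain is also easy to overstate. The rise from 32% to 53% needs all four effects to be real and of equal size, and section 2.12 does not make confirming all four a criterion of success. With two real effects the gain in average power is only about 2 points, and with one there is none. The value 0.63 comes from another trial's FS-14 result. In favour of the change, section 2.3 does hypothesise benefit in every secondary domain, which is where the gain is largest. A hypothesis is not evidence of effect size, however.

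Finally, Holm is not better in every respect. Bonferroni yields simple simultaneous intervals that agree with its tests, and Holm does not. That is a real but small drawback here, since section 2.12 plans no such intervals.

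**Conclusion.** This is a cheap, optional improvement. For rejecting secondary null hypotheses at a guaranteed family-wise level of 0.05, Holm is never worse than the named method and is sometimes better. With four outcomes, 40 per arm, correlation 0.5 and d = 0.63 per real effect, the gain in average power is about 9 points if all four effects are real, 5 if three, 2 if two and none if one. It is about 7 points at d = 0.5 with all four real. Family size, effect sizes and correlation are all assumptions.

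A reader might also infer that the trial's main conclusion or its size is weakened. The documents do not support that: the correction is tied to "simultaneous evaluations of multiple secondary outcomes", and the FS-14 comparison and the 90 patients stay as they are.

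**What to change.** In section 2.12, replace the Bonferroni correction by the Holm step-down correction for the same family of secondary outcomes, and document the change before unblinding. Section 2.2 schedules the trial to 30 November 2026.

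The cost is one sentence. Holm needs only the ordered p-values, with no change to data collection, sample size or the primary analysis. If unadjusted 95% confidence intervals are reported beside Holm-adjusted p-values, label them as unadjusted, because an interval may exclude zero when the adjusted test is not significant.

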## Discussion

3

CFS has become a significant global public health concern, characterized by an increasing incidence that profoundly affects patients’ physical and mental well-being, as well as their overall quality of life (30, 31). While moxibustion has been shown to effectively mitigate various symptoms associated with CFS, traditional moxa box moxibustion may have a limited ability to improve overall clinical outcomes. In pursuit of a more efficacious therapeutic approach, we have designed this trial.

Jianqiao ancient moxibustion and moxa box moxibustion share similarities in their operational methodologies, as both techniques utilize two moxa sticks to deliver thermal stimulation to the circular periacupoint area. However, they differ in moxa composition and stick size, which can lead to variations in their stimulatory effects. Specifically, moxa box moxibustion employs pure moxa, whereas Jianqiao ancient moxibustion incorporates a compound of southern herbs (“Jian Shiba”) and northern moxa. This formulation is purported to warm yang without depleting body fluids, clear heat without causing cold stagnation, and eliminate wind-phlegm without inducing dryness, thereby enhancing its efficacy in warming and tonifying yang-qi (19). Furthermore, regarding the stick diameter, moxa box moxibustion uses 1.5-cm sticks, whereas Jianqiao ancient moxibustion uses 7-cm sticks. The larger size of the moxa sticks in Jianqiao ancient moxibustion is likely to result in a broader effective action range, deeper tissue penetration, and stronger therapeutic stimulation compared with moxa box moxibustion.

Acupoints serve as the loci for the ingress, egress, and accumulation of meridian qi and blood. Stimulation of these acupoints can facilitate the unblocking of meridians and modulate visceral functions (32). In this study, we selected CV4, BL23, BL20, BL21, BL31, BL32, BL33, and BL34 as the intervention acupoints. Specifically, moxibustion at CV4 is employed to warm the middle jiao and address deficiency (33), whereas BL23 is utilized to tonify kidney qi and alleviate consumptive fatigue (34). In alignment with Zhang Zhongjing’s recommendation to treat consumptive diseases primarily by regulating the spleen and stomach (35), BL20 and BL21 are applied to activate the middle jiao, enhance spleen–stomach qi, and replenish primordial qi (36, 37). In addition, moxibustion on BL31–BL34 is intended to nourish kidney yang and kidney essence (38). Consequently, the combined moxibustion at these acupoints is anticipated to yield yang-warming and deficiency-tonifying effects, thereby mitigating symptoms of CFS.

Fatigue is the primary symptom associated with CFS; therefore, the FS-14 will be used to assess the potential of the intervention in reducing the severity of fatigue experienced by patients. Beyond persistent fatigue, individuals with spleen–kidney yang deficiency often exhibit distinct TCM clinical manifestations, including aversion to cold, lumbosacral soreness and weakness, lassitude, and reduced food intake. Therefore, the Spleen–Kidney Yang Deficiency Symptom Scale will be employed to quantitatively evaluate the overall improvement in clinical symptoms associated with this TCM syndrome. Additionally, anxiety and depression are prevalent among patients with CFS, potentially exacerbating physical symptoms and negatively impacting clinical outcomes (39, 40). As such, the SDS and SAS will be used to assess the intervention’s effect on these negative emotional states.

Furthermore, this study aims to analyze the variations in the infrared thermal imaging characteristics of the Sanjiao and Governor Vessel before and after treatment. The Sanjiao plays a crucial role in the production, transformation, and distribution of qi, blood, body fluids, and essence, facilitating their upward, downward, outward, and inward movement. Through the transformation of qi by the Sanjiao, the zang-fu organs are interconnected, thereby regulating bodily functions and supporting all vital activities of the human body (41). In healthy individuals, the Sanjiao maintains a stable temperature rhythm, typically exhibiting an orderly gradient with a cooler upper jiao, a moderate middle jiao, and a warmer lower jiao, thereby preserving the physiological equilibrium of a cool upper and warm lower jiao (42). The Governor Vessel, often referred to as the “sea of all yang meridians,” plays a crucial role in regulating yang-qi throughout the body. It traverses the posterior midline and establishes a connection with the kidneys, thereby accumulating yang-qi to nourish internal organs and serving as a primary conduit for the transport of essence (43). Consequently, the surface infrared temperature and continuous thermal profile of the Governor Vessel can serve as indicators of whether systemic yang-qi is both sufficient and unobstructed (19, 44). Patients suffering from CFS typically exhibit distinct features in infrared thermal imaging, such as significant thermal deviations in the upper jiao, cooler deviations in the middle jiao, and a lack of continuity in the thermal line of the Governor Vessel (45). Therefore, detecting the infrared thermal characteristics of the Sanjiao and Governor Vessel can provide an objective assessment of the regulatory effects of moxibustion on yang-qi distribution and meridian thermal balance, while also offering insights into its underlying mechanism in the treatment of CFS.

Nevertheless, this trial is subject to several limitations. First, due to the distinct differences in operational methodologies and appearance between the Jianqiao ancient moxibustion and moxa box moxibustion interventions, it is not feasible to achieve complete blinding of therapists and participants. This limitation may introduce performance bias. To mitigate such bias, all outcome evaluators and statisticians will remain blinded throughout the trial process. Second, the study is a single-center trial with a relatively small sample size, which may limit the generalizability of the findings to broader populations and different clinical settings. Future research should consider multicenter trials with larger sample sizes to enhance validation. Third, this trial will exclusively recruit patients with CFS exhibiting a spleen–kidney yang deficiency pattern. Other prevalent TCM patterns, such as liver stagnation and spleen deficiency, heart-spleen deficiency, and internal dampness-phlegm retention, are not addressed. Consequently, the results cannot be generalized to CFS patients with other syndrome types.
